### **4.1 Screening (Day 1, Visit 1)**

All screening assessments including randomization and patient enrollment are to be performed within 36 hours. Informed consent is to be obtained from each patient prior to any study-related procedures. After obtaining informed consent, the following assessments will be performed prior to initiation of study drug infusion on Day 1 (Visit 1):

- Review of inclusion/exclusion criteria.
- Review of demographic and baseline characteristics.
- General physical and otolaryngological examination including otoacoustic emissions, tympanometry, stapedius reflex measurements
- Vital signs.
- Review of medical history as well as previous medication (all medication taken within the last 30 days prior to Visit 1) and concomitant medication.
- Pregnancy test.
- Audiometric evaluation (PTA and speech intelligibility test inclusive word recognition).
- Occurrence and severity of tinnitus
- Vertigo evaluated using video- or electronystagmography or Frenzel goggles.
- Patient assessment of change in hearing impairment assessed using NRS
- Physician assessment of change in hearing impairment assessed using NRS
- Biomarkers (see Section 8.2.1).

|                                |                             |                      |
|--------------------------------|-----------------------------|----------------------|
| Protocol Amendment 7.1         | Study no.: NM-V-101         | Page 28 of 85 |
| Date of Amendment: 15 Feb 2018 | EudraCT No.: 2012-000066-37 |                      |

- Blood sample for neutralizing anti-ancrod-antibodies
- Safety laboratory assessments including coagulation, hematology, clinical chemistry, and urinalysis (for details see Section 8.2.2).

Immediately after randomization, patients will receive the initial administration of study drug (active or placebo) as intravenous infusion on the first day of treatment. The initial dose of study drug will be adjusted according to the screening fibrinogen concentration by using different infusion durations at a constant infusion rate (see Section 7.1).

All screening assessments including randomization and patient enrollment are to be completed within 36 hours.

AEs will be recorded starting from initiation of study drug infusion.

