The mean changes in PTA will be compared for the following subgroups:

- Gender (males or females)
- Degree of SSHL
- SSHL with or without associated vestibular symptoms
- Presence of tinnitus
- Age (above vs. below median, quartiles)
- Status of the contralateral ear
- Duration of SSHL before start of treatment (above vs. below median)
- Baseline fibrinogen level ( $\leq 360$  mg/dL;  $>360$  mg/dL, quartiles)
- Use of rescue medication.

In addition, the effect of diabetes mellitus, hypertension, and ischemic heart disease will be included in the analysis.

Because the study is not powered to detect significant treatment effects in subgroups, the limitations of drawing conclusions if no treatment effect is observed in a subgroup is recognized.

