Data source for prior and concomitant medications are all findings being recorded in the CRF module "Concomitant Medication" located in the CRF for each study visit.
- A flag variable will be derived to indicate the status of laboratory values:  
*Conversions* to the standardized unit are marked in listings by a '&' sign.  
A value *below* the lower limit of the normal range (LLN) will be indicated by a '<' mark;  
a value *above* the upper limit of the normal range (ULN) will be indicated by a '>' mark.  
Normal ranges are available only for lab values provided by the central lab (as part of the transferred data) and will be used for flag derivation; for lab values from local laboratories as entered in the CRF no normal ranges are available.

- A flag variable will be derived indicating visits or *assessments being out of the scheduled time frame* by '#'. The following time frames will be used to identify out-of-range assessments:
  - Screening (Visit 1): Start time of visit is earlier than 36 hours before the start time of first study infusion
  - Visit 2, Day 2): Not on study Day 2
  - Visit 3 (Day 4): Not on study Day 4 or 5
  - Visit 4 (Day 6): Not on study Day 6 or 7, or the day before Visit 4 is a day with IMP dose
  - Visit 5 (Day 8): Not on study Day 7 to 9, or the day of Visit 5 is a day with IMP dose
  - Visit 6 (Day 30): Earlier than Day 23 or later than Day 37
  - Visit 7 (Day 90): Earlier than Day 83 or later than Day 97.Deviations from the visit schedule represent a protocol deviation and are reviewed at the BDRM to determine their consequence.

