#### **5.7. Examination of Subgroups**

The patient subgroups as defined in Section 4.2 will be evaluated descriptively for the following study variable:

- Change in PTA (Air) in the affected ear from Visit 1 to Visit 5 (see Section 9.1.1).

In addition, to assess the relevant risk factors, a step-down analysis of covariance (ANCOVA) model will be established on above study variable that initially includes the subgroups of Section

4.2 (but not subgroups based on quartiles and the subgroups for rescue medication use) and the following factors at Visit 1:

- Biomarkers (CD38+ and CD42+ cells, interleukin-6, TNF- $\alpha$ )
- Frequencies affected by SSSL (high-tone, low-tone, pantonal, unspecified)
- Diabetes mellitus (yes, no)
- Hypertension (yes, no)
- Ischemic heart disease (yes, no).

Diabetes mellitus, hypertension and ischemic heart disease will be identified during the BDRM based on the entries for physical examination at Visit 1.

In a first step, all variables with low influence ( $p > 0.5$ ) will be removed. From the resulting model, successively the factor with lowest influence will be eliminated until a model remains that contains only the significant influence factors ( $p < 0.05$ ).

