### 7.3. Previous and Concomitant Diseases

N/A – diseases are not captured explicitly in the CRF.

Findings of the general physical examinations include diseases and are analyzed as described in Section 10.5.

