#### **10.5. General Physical Examination**

A physical examination is performed at Screening (Visit 1) to document the patient's medical history and at Day 8 (Visit 5) to document changes since Screening.

Separately for each body system listed in the CRF, the categories at Screening ('Not done', 'Normal', 'Abnormal') and at Day 8 ('Not done', 'No change', 'Change') will be given in a frequency table. Any specifications for abnormality and change will be presented in a patient data listing.

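### SAP 5.7 identifies diabetes, hypertension and ischemic heart disease from Visit 1 physical-examination entries alone, so treated disease with a normal examination may be coded 'no' in the exploratory risk-factor model

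*Combined protocol and SAP*

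**What the plan says.** Protocol 10.2.1 (additional analyses of the primary outcome) asks that "the effect of diabetes mellitus, hypertension, and ischemic heart disease will be included in the analysis", without naming a data source. SAP 5.7 turns the three conditions into yes/no factors in a step-down ANCOVA on the Day 8 change in air-conduction PTA, and gives the source: "Diabetes mellitus, hypertension and ischemic heart disease will be identified during the BDRM based on the entries for physical examination at Visit 1".

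Three other places describe what those entries contain.

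- SAP 7.3 says that "diseases are not captured explicitly in the CRF", and then adds: "Findings of the general physical examinations include diseases and are analyzed as described in Section 10.5".
- SAP 10.5 gives the purpose of the Visit 1 entry: "A physical examination is performed at Screening (Visit 1) to document the patient's medical history". For each body system the form records not done, normal or abnormal, and any abnormality is specified in a listing.
- Protocol 8.1.2 gives a minimum list of systems. It has cardiovascular and neurologic headings, among others, and ends with other examinations. It has no endocrine or metabolic heading.

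Medication is collected separately. Protocol 4.1 asks for medical history and for all medication taken in the 30 days before Visit 1. SAP 4.3 states: "Data source for prior and concomitant medications are all findings being recorded in the CRF module" for concomitant medication, completed at each visit. SAP 4.4 and 7.4 code these records and summarize them by ATC class. SAP 5.7 does not refer to them.

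**The concern.** The entry format invites under-recording of controlled disease. A patient with well-treated hypertension, tablet-controlled diabetes or stable coronary disease can have a normal cardiovascular and general examination. Nothing in the SAP says that such a diagnosis must still be entered, and diabetes has no obvious line. SAP 5.7 then leaves the yes/no decision to the meeting without a definition or a cross-check.

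Eligibility sharpens this. Protocol 5.1.3 excludes several overt presentations, such as recent unstable angina, diabetic retinopathy and diastolic pressure above 105 mmHg. The comorbid patients who can enter are therefore more likely to be mild or controlled cases.

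At stake is the reading of three factors that the protocol asks for in a trial with a vascular rationale. If affected patients sit in the 'no' group, the contrast shrinks and the 'yes' group loses members. The step-down first removes factors with p above 0.5, so a factor could drop out and a reader could not tell absence of effect from missed cases.

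**Working it through.** **The plan's own figure.** The documents give no figure for comorbidity. The only related number is the sample size, which reproduces. With a 15 dB difference, SD 20 dB, two-sided 5%, 90% power and 2:1 allocation, the placebo group needs (1 + 1/2) × (1.960 + 1.282)² × 20²/15² = 28.02, rounded up to 29. With 58 on ancrod the total is 87, and 87/0.88 = 98.9 gives 99. Comorbidity plays no part in it.

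**Where the factors enter.** The primary model (SAP 5.2 and 9.1.1) has treatment, center and baseline PTA. The three conditions are not among the SAP 4.2 subgroups and are not named in the SAP 9.1.1 regression. They appear only in the SAP 5.7 step-down model, so any miscoding stays there.

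**Size under assumptions.** The documents give neither the prevalence p of each condition nor the sensitivity s of the entries. Both are assumed below, with no false positives. I take n = 33, because SAP 2 expects only a few more than 30 evaluable patients.

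- Share of the coded-'no' group that truly has the condition: p(1−s)/(1−ps).
- Retained contrast: 1 minus that share, which equals (1−p)/(1−ps).
- z ratio against correct coding: retained contrast × √[1/(np) + 1/(n(1−p))] / √[1/(nps) + 1/(n−nps)].

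Worked case, p = 0.30 and s = 0.60: 5.94 of 9.9 affected patients are coded 'yes'. The contaminated share is 0.12/0.82 = 0.146, so 0.854 of the contrast is retained, and the z ratio is 0.854 × 0.838 = 0.72.

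| p | s | coded 'yes' / truly affected | contrast retained | z ratio |
|---|---|---|---|---|
| 30% | 30% | 3.0 / 9.9 | 0.77 | 0.48 |
| 30% | 60% | 5.9 / 9.9 | 0.85 | 0.72 |
| 30% | 90% | 8.9 / 9.9 | 0.96 | 0.93 |
| 10% | 30% | 1.0 / 3.3 | 0.93 | 0.53 |
| 10% | 60% | 2.0 / 3.3 | 0.96 | 0.76 |
| 10% | 90% | 3.0 / 3.3 | 0.99 | 0.94 |

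Most of the loss comes from the smaller 'yes' group rather than from dilution: in the worked case the group-size term is 0.838 and the retained contrast 0.854, but at 10% prevalence and 60% sensitivity they are 0.79 and 0.96.

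**Power.** Assume a true 15 dB comorbidity effect, SD 20 dB, n = 33 and a two-group t-test. At 30% prevalence with full capture, the standard error is √(400/9.9 + 400/23.1) = 7.60 dB, the noncentrality is 15/7.60 = 1.97 and power is about 48%. With half the cases found, the observable difference is 15 × 0.824 = 12.4 dB, the standard error is about 9.8 dB, the noncentrality is 1.26 and power is about 23%. At 10% prevalence the two powers are about 24% and 14%.

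**A rule that is too loose also loses information.** Suppose a patient is coded 'yes' if any source is positive, with an assumed 95% sensitivity and 85% specificity. At 10% prevalence the coded-'yes' share is 0.095 + 0.135 = 0.23, of whom 0.095/0.23 = 41% are true cases. The retained contrast is 0.413 − 0.0065 = 0.41, and the z ratio is 0.41 × √(0.23 × 0.77)/√(0.10 × 0.90) = 0.57. That is worse than the 0.76 for entries that find 60% of cases with no false positives. At 30% prevalence the same rule gives 0.75 against 0.72, about equal.

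**The case against.** The strongest reply is that SAP 5.7 already points to the right record. SAP 10.5 makes the Visit 1 entry the place for medical history, and SAP 7.3 says that the findings include diseases. A reader might infer from the format that these entries miss controlled disease. The documents do not show that; they show only that nothing prevents it. This part of the reply stands, and the point is therefore worded as a possibility.

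The missing endocrine heading proves little by itself. The protocol's list is a minimum with an open last item, and SAP 10.5 follows the systems printed in the CRF, which is not among the documents.

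The arithmetic also has limits. It is a two-group contrast, whereas the step-down model starts with about 23 coefficients by my count (13 from the eligible SAP 4.2 subgroups if every category occurs, 4 biomarkers, 3 for affected frequencies, 3 comorbidities) on some 33 patients. Even with perfect capture, power was only about 48% in the favorable case above. A reader might infer that a null result would be caused by the coding rule; small numbers would be the larger cause. Ischemic heart disease may also be rare here, because Protocol 6.4.1 bars users of antiplatelet drugs and anticoagulants.

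Finally, SAP 4.5 already brings medication listings to the meeting. They are there to find protocol deviations, however, and SAP 5.7 does not direct anyone to use them for these factors.

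**Conclusion.** The point holds as a minor gap. SAP 5.7 gives three factors required by the protocol a single source, without a case definition, in a format where treated disease with a normal examination may go unrecorded. A coded second source already exists and is not used.

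The effect is confined to the comorbidity terms of one exploratory model. A reader might infer that the treatment effect on the primary PTA change is diluted; it is not, because the confirmatory model has no such term.

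The size is unknown. The z ratios of 0.48 to 0.94 rest wholly on assumed prevalence (10% and 30%), assumed sensitivity (30% to 90%), perfect specificity and 33 patients. They show how the loss would behave, not how large it is in this trial.

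**What to change.** In SAP 5.7, replace the sentence on identification. State that at the blind data review meeting, before unblinding, each condition is identified from the Visit 1 physical-examination or medical-history entries together with the coded prior and concomitant medication listing (for example antidiabetics, antihypertensives and antianginals). Add that each case supported by medication alone is decided blind and the reason minuted, because some drug classes serve several indications.

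Screening blood pressure and glucose may be shown beside the listing as supporting information, but should not by themselves code a patient 'yes'. The SAP 10.7 limits are shift-table normal ranges based on one reading, and the calculation above shows how quickly false positives can cancel the gain when a condition is uncommon.

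The cost is one changed sentence, one extra blinded listing and a little more time at the meeting. No new data are needed and the primary analysis does not change. An occasional false 'yes' will remain.

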## 6. Study Population Characteristics

All statistical tables described in this chapter will show aggregated data by treatment group and overall.

### 6.1. Population Overview

Frequency tables will be prepared presenting the number of patients randomized, eligible (i.e., meeting all inclusion criteria but none of the exclusion criteria), and treated. Moreover, the following information will be given for all patients randomized:

- The date of the FPI (date of informed consent)
- The date of first patient's first IMP intake
- The date of last patient's last treatment
- The date of the LPO (date of last documented visit).

Reasons for exclusion from any analysis population will be shown in a patient data listing.

For all patients randomized, the following information will be summarized in a frequency table:

- The number and percentage of patients completing the trial [1] and of those who terminated the trial prematurely ('Dropouts')
- The number of patients with unblinding performed
- The number of patients per study center
- The patient disposition by visit (attended/missed).

[1] 'Completers' are patients with the answer 'Yes' to the question 'Regular end of observation?' on the CRF's End of Study form.

The reason for leaving the study (applies to dropouts only) will be given in a patient data listing.

### 6.2. Protocol Deviations

The number of patients who are member of the SFS, FAS and PPS will be included in a frequency table together with the number and percentage of all randomized patients with

- at least one deviation from the study protocol
- at least one major deviation

- at least one minor deviation but no major deviation.

In addition, the number and percentage of all randomized patients with major deviations will be summarized by type of deviation. Correspondingly, the number and percentage of all randomized patients with minor deviations will be summarized by type of deviation.

A patient data listing will be prepared displaying each randomized patient's protocol deviations.

### 6.3. Patients Excluded from Analysis Populations

The BDRM meeting minutes depict all patients excluded from any analysis set as determined during the BDRM. A patient data listing will be prepared displaying for patients excluded the reason(s) for exclusion.

## 7. Demographics and Other Baseline Characteristics

Demographic characteristics and other baseline/background data as listed below will be evaluated descriptively for the SFS, FAS, and PPS; all results will be given by treatment group and overall.

### 7.1. Demographics

Summary statistics or frequency tables will be computed for age, sex, and BMI. Age will be tabulated in addition with the categories <18 years, 18 to 30 years, >30 to 50 years, >50 to 70 years, and >70 years.

### 7.2. Disease Characteristics

The following data from the Screening visit will be summarized to describe the underlying study conditions:

- Duration of SSHL (days) – summary statistics
- Affected ear (right ear, left ear) – frequency table
- Occurrence of tinnitus (yes, no) – frequency table.

All other disease characteristics recorded in the CRF will be included in the evaluation of efficacy variables.

### 7.3. Previous and Concomitant Diseases

N/A – diseases are not captured explicitly in the CRF.

Findings of the general physical examinations include diseases and are analyzed as described in Section 10.5.

### 7.4. Prior and Concomitant Medications

For the definition of prior and concomitant medications, refer to Section 4.3. Recorded treatments are coded by medication groups as described in the DMP. The allocation of reported terms to higher-level classifications is made using the preferred ATC code.

Prior and concomitant medications will be summarized separately using Level 2 (3-digit) and Level 3 (4-digit) of the ATC code. Frequency tables will be generated on a patient basis: Patients are counted only once for each ATC class when they have more than one medication within the same ATC class. Patients with more than one medication within a level 2 ATC class will be counted for each corresponding level 3 term, but only once for the level 2 class. The number and percentage of patients with at least one medication reported will also be displayed. All tabulations will be sorted alphabetically by level 2 ATC decode and by frequency of level 3 decodes within level 2 class.

Specific findings on medications will be presented in a corresponding patient data listing.

### 7.5. Other Baseline Characteristics

For female patients, birth control data from Visit 1 (pregnancy test performed yes/no and result) will be listed only.

## 8. Study Treatments

### 8.1. Exposure to IMP

To describe IMP exposure during study, the following summary tables will be presented by treatment group for the SFS, FAS, and PPS:

- Number of study drug administrations (intravenously and subcutaneously separately)
- Total amount of IMP given (I.U. by administration and overall).

### 8.2. Study Compliance

N/A – as the study treatment is applied via infusion or injection at the site, consideration of compliance will not be meaningful.

### 8.3. Rescue Medication

Corticosteroids, vasodilators, vitamin C, vitamin B12 or antihistamines are allowed if deemed necessary at the discretion of the investigator, if, on Day 8, no improvement or worsening of symptoms has been observed. Rescue medication among the concomitant medications will be identified in the BDRM and will be analyzed in analogy to the evaluation of concomitant medications presented in Section 7.4.

## 9. Efficacy Analyses

The primary analysis of all efficacy variables will be based on the Full analysis set (FAS). For the following efficacy variables, the evaluation will be repeated for the PPS as sensitivity analysis:

- Change in PTA (Air) in the affected ear from Screening to Day 8 (primary efficacy variable)
- Change in PTA (Bone) in the affected ear from Screening to Day 8, Day 30 and Day 90
- Change in PTA (Air) in the affected ear from Screening to Day 30 and Day 90
- Change in word recognition score from Screening to Day 8, Day 30 and Day 90.

Besides descriptive analyses, inferential statistics will be computed that are confirmatory for the primary efficacy variables and of explorative nature only for all secondary variables. All statistical tables will show data aggregations by treatment group but not for overall.

### 9.1. Change in PTA (Air) from Visit 1 to Day 8 (Primary Efficacy Variable)

A pure tone audiogram (PTA) is conducted for each ear separately at Screening (Visit 1), Day 8 (Visit 5), Day 30 (Visit 6), and Day 90 (Visit 7). Auditory thresholds for the methods 'PTA Air' and 'PTA Bone' are recorded in the CRF for the frequencies 0.125, 0.25, 0.5, 1, 2, 4, 6, and 8 kHz.

In a first step, the audiograms (right ear, left ear) for air conduction at Screening will be compared to identify the ear affected by SSHL and the affected frequencies (a decrease of  $\geq 20$  dB in the affected ear compared to the contralateral ear).

$$\text{Change in PTA} = \text{treatment} + \text{center} + \text{PTA at Visit 1.}$$

Underlying assumptions, such as normality and homogeneity of variance, are assessed at the BDRM. Should these assumptions be violated, appropriate data transformations or the choice of a non-parametric analysis method will be considered.

In addition, the mean change at the affected frequencies will be classified into the following categories and evaluated in a frequency table using the Freeman-Halton test:

| Definition* | Improvement                                                                                                                                                                                                            |
|-------------|------------------------------------------------------------------------------------------------------------------------------------------------------------------------------------------------------------------------|
| Recovery    | Hearing level recovers within 30 dB at 250, 500, 1000, 2000 Hz and within 25 dB at 4000 Hz, or
Hearing level recovers to that of contralateral intact ear if hearing in intact ear can be considered to be stable** |
| Good        | Average hearing improvement for the five frequencies $\geq 30$ dB                                                                                                                                                      |

|           |                                                                                 |
|-----------|---------------------------------------------------------------------------------|
| Fair      | Average hearing improvement for the five frequencies $\geq 10$ and $\leq 30$ dB |
| No change | Average hearing improvement for the five frequencies is within 10 dB            |

\* Hearing recovery as defined by the Ad Hoc Committee of the Ministry of Health and Welfare in Japan

\*\* The contralateral intact ear is regarded as stable when threshold values for Visit 1 and Visit 5 differ at most by 10 dB.

Besides, a comparison of mean changes of participants who completed the study will be made: Multiple linear regression analysis will be performed to evaluate the magnitude of the treatment effects after adjustment for participant characteristics such as age, duration of SSHL prior to treatment, and baseline degree of hearing loss (mild  $\leq 30$  dB; moderate to profound  $> 30$  dB).

Moreover, for the subgroups defined in Section 4.2, the mean changes in PTA will be analyzed for the FAS as described in Section 5.7.

